### Procedure

All knee injuries from the PTs patient pool are reported to the SC during weekly contact, in which the SC reminds PTs of inclusion criteria and actively seeks information on knee-injured participants in order to approach all potential participants in the patient pool. The number of patients approached and invited (i.e., eligible, ineligible, and declined participation) will be recorded. The SC contacts potential participants that have consented to a pre-screening interview, during which information is provided, inclusion, and exclusion criteria are verified, and, if eligible, the participant is invited to take part in the study. Information provided to potential participants includes only that there is a “mental training intervention” with no details which could be used to replicate the intervention, adhering to Swedish ethical guidelines for participant informed consent. Following pre-screening, the SC has regular contact with participants and physical therapists in order to receive updates on patient progression through rehabilitation. This ensures proper inclusion timing and reduces the risk of late inclusion by reducing dependency on physical therapists with regard to inclusion criteria, as well as ensuring that eligible participants are included in the trial. Rehabilitation during this period is provided according to rehabilitation protocols prescribed at the discretion of the PT until the participant is able to complete single-leg hop tasks, ensuring proper inclusion timing. When the hop ability criterion is confirmed by the PT, written information is provided, and baseline testing takes place, during which the test leader collects informed consent (Additional File 3 – Informed Consent Materials). The intervention then begins, implementing either CaU or MOTIFS training in the clinical setting during treatment. The intervention period is 12 weeks, as studies have shown that physical [28] and psychological [29] factors can be improved in this time span. MOTIFS training accounts for approximately 20 min [30] in a typical 60-min training session. At least 3 supervised or at-home training sessions are performed per week, whereof at least 6 are supervised by a participating PT during the intervention period, resulting in an intervention dose of 36 possible training sessions, with intensity prescribed by the PT. Participants and PTs are made aware of the possibility to end their involvement in the study. Participants may remove themselves at their discretion, or worsening symptoms may require the PT to change treatment strategy. To ensure that participants complete self-report questionnaires, telephone contact may be initiated.

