#### Main outcomes

This trial includes two main outcomes. Psychological readiness to return to sport is evaluated using the Swedish version of the ACL-Return to Sport after Injury scale (ACL-RSI), which includes an emotional response, confidence, and risk-appraisal when returning to sport after an ACL injury [33, 34]. Physical function is evaluated using the change in number of hops in the injured leg from baseline to 12 weeks for the side hop task.

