##### Hop test battery

The hop test battery [6], consisting of two functional tasks (single-leg hop for distance and side hop) performed on both legs, is used to evaluate muscle function. The single-leg hop for distance is done by standing on one leg and performing a maximal jump forward, landing with control on the same leg, and maintaining control for 2–3 s. Failure to maintain landing position results in a disqualified hop and the hop will be repeated. The side hop task is performed by jumping on one leg from side to side over two parallel lines taped 40 cm apart on the floor as many times as possible in 30 s [44]. The number of successful hops without touching the line is recorded. Results are expressed as change in the injured leg, change in the uninjured leg, and limb symmetry index (LSI; LSI = (injured leg/uninjured leg) x100) individually and summed.

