### Statistical analyses

#### Sample size

Based on previous studies examining ACL-RSI [49] and side-hop function [50], a preliminary sample size was estimated, to be used in the first phase of this adaptive RCT, which resulted in *n*=106 participants. This included adjustments for potential cluster effects using a preliminary Intra-Cluster Correlation Coefficient (ICC). An approximation is required as comparable studies are unavailable to reliably perform a sample size estimation. This is necessary in this phase in order to evaluate whether an intervention effect is detectable and within practical limitations, which will thereafter inform more accurate sample-size estimations.

A new sample size will be calculated by a blinded third-party member of the data management committee using collected data from an interim analysis, therefore allowing for more accurate between-group differences in the main outcomes. Observed within- and between-cluster variance will also be calculated in order to more accurately estimate an Intra-Cluster Correlation Coefficient (ICC, denoted as *ρ*). This will be performed using the formula $$ \rho =\frac{s_b^2}{s_b^2+{s}_w^2} $$ [51] in order to adjust for the fact that different clinics are included in the trial (i.e., potential clustering effects). The adjusted sample size will therefore be calculated using the formula $$ \frac{n_ik\left(1-\rho \right)}{k-{n}_i\rho } $$ [52], along with an estimated 20% drop-out rate, in order to reach a power of 0.80, with significance set at *p*<0.025. As an estimated sample size has been calculated, the new sample size will only be adjusted up; that is, the number of participants included will not be less than *n*=106 required in the original sample-size estimation.

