#### Data analysis

The analysis will be done using the IBM SPSS statistical software package (IBM Corp., Armonk, New York, USA). Primary analyses of the entire sample will be done according to intention-to-treat principles. A dose-response analysis will be performed to determine effective adherence. Per-protocol analyses will be performed for those participants with at least 70% adherence (corresponding to two trainings per week), as a preliminary estimate of the effective number of training occasions. This is in order to eliminate cross-over and drop-out effects in the total sample, as well as to evaluate the training for those that have reached a pre-defined level of adherence deemed acceptable to have an effect. Sensitivity analyses will be performed to determine whether within-cluster correlations indicate potential effects due to being clustered, for example, by the clinic or by PT. Patient cross-over (i.e., patients changing clinics) is a low-risk possibility and will be recorded in case of occurrence. All outcome variables will be examined for normality using appropriate testing (e.g., Kolmogorov-Smirnov). Complete-case analyses are the primary analyses, and sensitivity analyses will be done depending on the number of missing values. Missing values are not expected to be extensive, and if less than 5% of data is missing, the whole data set will be analyzed along with a sensitivity analysis with appropriate imputed values. If between 5 and 40% of data is missing, appropriate multiple imputation methods will be used, which will be informed by blindly assessing results of the interim analysis, and a complete-case analysis will be done with appropriate sensitivity analyses. If over 40% is missing, a complete case analysis will be done with no sensitivity analysis.

Results will be analyzed using independent samples *t* tests to examine between-group differences of the change from baseline to a 12-week follow-up. Where appropriate, equivalent non-parametric Wilcoxon signed-rank testing will be used to compare between-group differences. The main analysis will focus on the two main outcomes, with secondary outcomes acting as support for these. Secondary outcomes therefore carry less weight and issues with potential error due to the number of evaluations will be discussed when results are presented.

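### Participants who do not attempt the week-12 side hop because of the study knee leave the primary complete-case comparison, and no planned analysis of that main outcome brings them back as a poor result

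*Protocol article*

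**What the plan says.** The Main outcomes section defines the physical main outcome as the "change in number of hops in the injured leg from baseline to 12 weeks for the side hop task". The Hop test battery section gives the scoring: "The number of successful hops without touching the line is recorded". It says nothing about a test that is not attempted.

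The Data analysis section makes two statements about the primary analysis. One is "Primary analyses of the entire sample will be done according to intention-to-treat principles". The other is "Complete-case analyses are the primary analyses", with sensitivity analyses that depend on how many values are missing. It then sets three bands:
- Below 5% missing: the whole data set is analysed, with an imputed sensitivity analysis.
- From 5% to 40%: multiple imputation by a method still to be chosen, plus a complete-case analysis with sensitivity analyses.
- Above 40%: complete cases only, with no sensitivity analysis.

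Knee deterioration after inclusion is foreseen. The Procedure section notes that participants may withdraw and that "worsening symptoms may require the PT to change treatment strategy". The Adverse events/harms section asks weekly about giving way, swelling, more pain, and a new knee injury that led to crutches or another operation. The Sample size section plans the recalculation "along with an estimated 20% drop-out rate", while the Data analysis section does not expect extensive missing data.

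**The concern.** Table 1 and the Procedure section require participants to have reached single-leg hop training, with hop ability confirmed by the physical therapist before baseline testing. So a week-12 side hop not attempted because of the knee is deterioration after inclusion. It is a bad result on this outcome, not an unknown one.

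Complete-case analysis treats it as unknown and removes it. The side-hop contrast then compares the arms only among people whose knees allowed the test. That is not the entire sample, and it is a fair comparison only if knee-related non-attempts are balanced. Participants and physical therapists are unblinded, so stopping or skipping the test may also depend on the arm. At stake is whether a reported side-hop benefit describes everyone allocated to MOTIFS or only those still able to hop.

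**Working it through.** **Is there enough missing data to matter?** The planned drop-out is 20%, and 0.20 × 106 = 21.2, so about 21 participants, or 10 to 11 of 53 per arm. That lies in the 5% to 40% band. The article does not give the share caused by the knee. The initial 106 cannot be rebuilt, because its effect size, SD, intra-cluster correlation and number of clusters are not printed. This point does not depend on it.

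**Closed form.** Let B be the mean baseline count, G the mean gain among those able to hop (equal in both arms, so no true effect), and p_M and p_C the proportions not attempting because of the knee. Assume inability is unrelated to the gain a participant would otherwise have had.
- Complete-case difference: G − G = 0, whatever p_M and p_C are.
- Imputation under missing at random: imputed gains centre on G, so the expected difference is again 0.
- Non-attempts scored as 0 hops: each has change −B, and the difference is −(p_M − p_C) × (B + G).

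**Assumed set 1** (no figure is from the article): B = 25 (SD 10), G = 8 (SD 8), so B + G = 33.
- 10% v 5% (MOTIFS v control): −0.05 × 33 = −1.65 hops.
- 15% v 5%: −0.10 × 33 = −3.3 hops.
- Equal rates: 0.

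Simulation of 4,000 trials with 53 per arm, ignoring clustering:

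| Not attempting, MOTIFS / control | Complete-case difference (SE) | Zero-scored difference (SE) |
|---|---|---|
| 5% / 5% | 0.0 (1.57) | 0.0 (2.08) |
| 10% / 5% | 0.0 (1.61) | −1.65 (2.31) |
| 15% / 5% | 0.0 (1.64) | −3.38 (2.52) |
| 10% / 10% | 0.0 (1.63) | 0.0 (2.49) |

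**Assumed set 2:** B = 20, G = 10, so B + G = 30. At 5% v 2% the zero-scored difference is −0.9; at 10% v 2%, −2.4; at 15% v 5%, −3.0; at 20% v 5%, −4.5. If MOTIFS participants able to hop gain 15, the complete-case difference is +5 throughout, while the zero-scored figure falls from +3.85 (5% v 2%) to −0.5 (20% v 5%): 0.80 × 15 − 0.20 × 20 = 8.0, against 0.95 × 10 − 0.05 × 20 = 8.5.

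The sign is symmetric. If the control arm had more non-attempts, complete-case would understate MOTIFS by the same formula.

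**Standardised size.** In set 1 at 15% v 5%, the zero-scored SE implies SD = 2.52 / √(2/53) ≈ 13.0, and 3.38 / 13.0 ≈ 0.26. At 10% v 5%, SD ≈ 11.9, and 1.65 / 11.9 ≈ 0.14.

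**Price of zero-scoring in a t test.** The variance ratio is (2.08/1.57)² ≈ 1.75 at 5% / 5% and (2.49/1.63)² ≈ 2.3 at 10% / 10%. With set 1, a true 5-hop effect among those able to hop, 5% not attempting in each arm and p < 0.025 two-sided, simulated power is about 0.80 for complete-case, 0.48 for the zero-scored t test and 0.7 for a worst-rank test.

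**The case against.** The strongest reply has four parts.

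First, the outcome is a count. A worsened knee that can still hop scores lower and already counts against its arm. A reader might infer that the outcome cannot be scored once a knee worsens, but the article does not support that. Nor does it say that a changed treatment strategy, swelling, pain or giving way prevents week-12 testing. Only non-attempts are at issue. A new injury with crutches or surgery is the clearest route to one, and even that need not last until week 12. This stands, and it limits the point.

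Second, harm is visible elsewhere. Knee events are recorded weekly and are a listed outcome, the interim analysis looks for harms, attrition analyses are planned, and ACL-RSI and KOOS can be completed by an injured participant. So the trial as a whole does not hide harm. But none of these puts a non-attempt into the side-hop contrast.

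Third, the article is condensed. A data collection form or analysis plan not shown may code an unable-to-perform test. That is fair as regards the missing scoring rule. It does not remove the conflict in the Data analysis section, where the entire sample and complete cases are both named as primary. Intention-to-treat read narrowly, as analysis by allocated arm, would fit complete cases, but the phrase about the entire sample would not. The imputation method is also left open, so a missing-not-at-random version is possible, but none is stated.

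Fourth, no passage shows that knee harm differs by arm. MOTIFS integrates imagery into exercises that the physical therapist prescribes in either arm. Table 2 adds sport-specific execution, which makes a difference conceivable, not likely. This stands.

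**Conclusion.** The point holds in a limited form. By making complete-case analysis primary, the protocol article removes knee-related non-attempts from the physical main comparison, and imputation under missing at random would not restore them as poor outcomes. If non-attempts are balanced, nothing is lost on average. If they differ, the side-hop result is silent about it. Under assumed hop values and rates, the unseen shift runs from 0 to about −3.4 hops, and to −4.5 in the most extreme assumed case. These figures are illustrations, not estimates for this trial.

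Two stronger readings fail. A reader might set −3.4 hops over the assumed SD of 8 and conclude that the shift exceeds the d of 0.1 to 0.3 in the plan's interim criteria. On the zero-scored scale it is about 0.26, and those d values are attached to ACL-RSI and limb symmetry, not to change in hop count. A reader might also conclude that a zero-scored t test should replace the primary test. The power loss shown above argues against that, and in the 15% v 5% case the zero-scored z is only 3.38 / 2.52 ≈ 1.34, so it would usually miss the harm as well.

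**What to change.** 1. In the Procedure and Outcome assessment sections, seek week-12 assessment of every participant, whether or not treatment was stopped or changed. Add a field for the reason when the side hop is not performed, separating the study knee from unrelated causes. Because participants and physical therapists are unblinded, define the categories in advance and have the blinded test leader record them.
2. In the Data analysis section, state that the complete-case and imputation results assume missingness unrelated to the knee, and reconcile this with the statement on intention-to-treat.
3. Prespecify for the side hop a whole-sample analysis, run at any level of missingness (so also above 40%), in which knee-related non-attempts count as 0 hops or worst rank, preferably with a rank-based test. Handle unrelated missing values separately, for example by imputation.
4. Report the number of non-attempts by arm and reason, and claim a side-hop benefit only if this analysis does not contradict the complete-case result.

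The cost is one form field, some extra follow-up effort and analysis, and a less precise supporting estimate. Attributing a non-attempt to the knee involves judgement, so the counts by reason should be shown beside the result.

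### The primary analysis is called both intention-to-treat on the whole sample and complete-case, and sensitivity analysis is withdrawn above 40% missing, where a result is easiest to overturn

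*Protocol article*

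**What the plan says.** The Data analysis section of the protocol article makes two statements about the primary analysis. Near its start: "Primary analyses of the entire sample will be done according to intention-to-treat principles". Further on in the same paragraph, where missing data are introduced: "Complete-case analyses are the primary analyses, and sensitivity analyses will be done depending on the number of missing values". Three bands follow.

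- Under 5%: "if less than 5% of data is missing, the whole data set will be analyzed along with a sensitivity analysis with appropriate imputed values".
- From 5 to 40%: "If between 5 and 40% of data is missing, appropriate multiple imputation methods will be used", with the choice of method to be informed by a blinded look at the interim results. The same sentence then adds that "a complete-case analysis will be done with appropriate sensitivity analyses".
- Over 40%: "If over 40% is missing, a complete case analysis will be done with no sensitivity analysis".

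The section expects little missing data, and it ends with a commitment to attrition analyses without further detail. The Sample size section says that the recalculated sample size will be worked out "along with an estimated 20% drop-out rate".

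**The concern.** Two things look wrong. First, a complete-case analysis drops everyone without a 12-week value, so it is not an analysis of the entire sample. A reader cannot tell for certain which estimate carries the conclusion on the two main outcomes, and the doubt is greatest in the band that holds the protocol's own drop-out allowance.

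Second, the amount of checking should rise with the amount of missing data, or at least not fall. Here it falls to nothing above 40%.

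The protocol itself makes outcome-related loss plausible. Participants and therapists are not blinded (Participants and randomization). Participants may leave when they wish, and worsening symptoms may lead the therapist to change the treatment strategy (Procedure). A new knee injury requiring crutches or surgery is among the events asked about each week (Adverse events/harms), and someone with such an injury may be unable to perform the side hop, which is a main outcome. If loss is related to outcome, completers in the two arms may no longer be comparable.

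**Working it through.** **1. Who is in the primary analysis.** The intention-to-treat sentence puts everyone in. The general missing-data sentence admits only those with outcome data. The under-5% rule refers to the whole data set and makes imputation the sensitivity analysis, which agrees with complete-case as primary if the whole data set means all observed data. The 5–40% rule names multiple imputation first and gives it no role. It then names a complete-case analysis and attaches separate sensitivity analyses to that. Two analysts could follow this rule and report different headline results.

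**2. Which band is likely.** The allowance is 20% (Sample size section). Applied to the planned 106 participants, 0.20 × 106 = 21.2, so about 21 would be lost. This lies inside 5–40%. The figure of 106 cannot be reproduced, because the article gives no planning difference, standard deviation, intra-cluster correlation value or number of clinics. Nothing below depends on it.

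**3. Bias of the complete-case contrast.** Let m be the share missing in each arm. The full-arm mean is (1 − m) × observed mean + m × missing mean. The complete-case mean therefore exceeds it by m × (observed mean − missing mean). The bias of the contrast is the MOTIFS term minus the CaU term. Assume, for illustration only, a gap of 0.5 SD between completers and leavers:

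| Pattern of departure | 20% missing | 45% missing |
|---|---|---|
| Same direction in both arms | 0.10 − 0.10 = 0 | 0.225 − 0.225 = 0 |
| One arm only | 0.2 × 0.5 = 0.10 SD | 0.45 × 0.5 = 0.225 SD |
| Opposite directions | 0.10 + 0.10 = 0.20 SD | 0.225 + 0.225 = 0.45 SD |

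**4. Departure needed to overturn a result.** Take a complete-case ACL-RSI difference of 5 points, which is the interim continuation criterion and is used here only as a yardstick. With departure in the MOTIFS arm alone, the difference vanishes when m × gap = 5, so gap = 5 / m:

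| Missing | Gap needed (ACL-RSI points) |
|---|---|
| 5% | 5 / 0.05 = 100 |
| 20% | 5 / 0.20 = 25 |
| 40% | 5 / 0.40 = 12.5 |
| 50% | 5 / 0.50 = 10 |

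At 5% missing the gap would have to equal the full width of the 0–100 scale. At 50% a tenth of the scale is enough. The plan requires a sensitivity analysis in the first case and rules it out in the last.

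**The case against.** The best defence reads the paragraph in order. The general sentence makes complete-case primary at every level, and the bands only say what goes with it. On that reading multiple imputation between 5 and 40% is the sensitivity analysis. The intention-to-treat sentence is set against a per-protocol analysis at 70% adherence, so it may mean only that participants are analysed as allocated, whatever their adherence. This is a natural reading. A reader might infer that the plan sets up two rival primary results with nothing to rank them; the general sentence means that the text does not go that far. What remains is that the 5–40% rule does not assign imputation that role, and that complete cases are still not the entire sample.

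Other points in the plan's favour also hold in part.

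- The 20% is a sample-size allowance, and the coordinator follows up missing questionnaires and data (Procedure; Data management). The 5–40% band is therefore likely rather than certain, and loss above 40% would be more than twice the allowance.
- The final analysis is done by a blinded third party, which limits choosing between results by their direction.
- Attrition analyses are promised. They can describe who left, but they do not test how the effect estimate depends on those who left.
- A reader might suppose that early return to sport drives drop-out. The protocol does not give it as a reason, and the exclusion criteria remove people expected to return within 12 weeks.

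Doubt about imputing when over 40% is missing is reasonable. It is a reason to limit the conclusion, not to report a complete-case result untested.

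**Conclusion.** The point stands as a conflict in stated text, together with one rule that runs the wrong way. Neither is detail left to a separate analysis plan. The conflict over the primary analysis is the more likely to matter, because it touches both main outcomes at the protocol's own allowance for drop-out. The over-40% rule is less likely to come into play, but it is plainly misdirected.

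The size depends on assumptions that the article cannot settle. With equal loss of 20% per arm and an assumed 0.5 SD gap, the bias runs from 0 to 0.20 SD. A reader might take 0.20 SD as the expected bias; it arises only if leavers depart in opposite directions in the two arms, and nothing in the article says they would. Nor should it be judged against the effect sizes of about 0.1–0.3 in the adaptive-design section as if those were the planning effect: they belong to exploratory continuation criteria that the authors themselves call theoretical. The firmer result is that the departure needed to remove a 5-point difference falls from 25 points at 20% missing to 10 points at 50%, given departure in one arm only.

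**What to change.** Before any outcome data by arm are seen:

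1. Name one primary analysis that agrees with the intention-to-treat statement and use it at every level of missingness. One option is all participants in the arm of their clinic, analysed by multiple imputation or by a likelihood-based model using arm, clinic and baseline value. Either is valid under missing-at-random.
2. Label the complete-case analysis as a sensitivity analysis in all bands.
3. Delete the rule that withdraws sensitivity analysis above 40%.
4. Require a delta-adjusted or tipping-point analysis whenever 5% or more is missing, above 40% included. Step 1 does not replace this: a missing-at-random analysis does not by itself address drop-out that depends on the unobserved outcome. Below 5% such an analysis adds little, as the 100-point figure shows.

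The cost is a rewritten paragraph and modest programming. No sample-size figure changes.

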## Methods

### Study design

The design of this study is a 1:1 single assessor-blinded cumulative adaptive cluster-randomized controlled trial, conforming to the Consolidated Standards of Reporting Trials (CONSORT) statement extension for pragmatic trials [25], with the intervention administered in real-world settings and conditions (trial pragmatism illustrated in Additional File 1). The cumulative adaptive design allows for modification upon evaluation of a subgroup in order to more accurately determine the required sample size, as well as whether changes need to be made to the method before the continuation of the trial [26]. Items from the World Health Organization Trial Registration Data Set are available on the ClinicalTrials.gov registration page (NCT03473821). This protocol adheres to the Standard Protocol Items: Recommendations for Interventional Trials (SPIRIT) guidelines [27], procedures of which are outlined in Fig. 1 (SPIRIT checklist available as Additional File 2). Ethical approval has been granted by the Regional Ethical Review Board in Lund, Sweden (Dnr 2016/413, Dnr 2018/927).

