### Participants and randomization

Approximately 106 participants are recruited according to inclusion criteria (Table 1) from physical therapy clinics in Sweden. Physical therapists (PTs) fulfilling inclusion criteria (Table 1) from these clinics are included in the trial. The eligibility criteria for both PTs and participants allow for the recruitment of a sample of knee-injured people and their PTs representative of the population. To avoid contamination, participating clinics are block randomized by a third party using a random numbers generator and sealed opaque envelopes to either the experimental or CaU condition.

**Table 1 Tab1:** Participant and physical therapist inclusion and exclusion criteria

Participants	
Inclusion	Exclusion
- Men and women 16 years or older - Traumatic knee injury (e.g., ligament, meniscal, patellar, or chondral injury), with or without surgical intervention, and involving one or more knee structures - Currently undergoing physical therapist-supervised rehabilitation training - Have reached the stage in their rehabilitation which includes single-leg hop training, as well as a change of direction - Active before the injury in recreational or competitive physical activity, with a goal of returning to physical activity	- Any degenerative knee disorder (e.g., osteoarthritis), or other disease or disorder (e.g., spine disorder, neurological disease) overriding the traumatic knee injury - Reached end-stage rehabilitation (i.e., have undergone a return to physical activity evaluation by their physical therapist, or is estimated to return less than 12 weeks from potential inclusion date) - Do not understand the languages of interest (Scandinavian languages, English)

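### Clinics are randomised, but the main test is an independent-samples t test that ignores clinic, so its false-positive rate exceeds 0.025 if outcomes correlate at all within clinics

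*Protocol article*

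**What the plan says.** - **Design.** Study design (Protocol article) describes a "1:1 single assessor-blinded cumulative adaptive cluster-randomized controlled trial". Participants and randomization says that "participating clinics are block randomized by a third party using a random numbers generator and sealed opaque envelopes", and explains that clinics are allocated instead of participants to avoid contamination.
- **Sample size.** Clustering is acknowledged for the total of 106: "This included adjustments for potential cluster effects using a preliminary Intra-Cluster Correlation Coefficient (ICC". The ICC is to be re-estimated at the interim and used to resize the trial, "along with an estimated 20% drop-out rate", "in order to reach a power of 0.80", "with significance set at *p*<0.025".
- **Analysis.** Data analysis states: "Results will be analyzed using independent samples *t* tests to examine between-group differences of the change from baseline to a 12-week follow-up". A non-parametric test is the fallback. Neither test has a clinic term.
- **Clustering in the analysis.** It appears once, as a secondary check: "Sensitivity analyses will be performed to determine whether within-cluster correlations indicate potential effects due to being clustered". Nothing says what follows if clustering is found, and nowhere is the main test or its standard error said to account for clinic.

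**The concern.** An independent-samples t test takes every participant as a separate, independent piece of evidence about the treatment. Here the pieces allocated to treatment were clinics. Patients at one clinic share therapists, facilities and local habits, and the article leaves the content of training to the therapist in both arms. Some resemblance within clinics in 12-week improvement is therefore plausible, and the sample-size section already plans for it.

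If that resemblance is positive, the t test understates the uncertainty of the arm difference. P values come out too low and confidence intervals too narrow for ACL-RSI and for side hop. A few clinics that happen to do well could produce a significant result with no effect of MOTIFS. The trial would also pay for clustering when it recruits and then analyse the data as if there were none.

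**Working it through.** **Inputs from the article.** Total 106 (53 per arm); significance 0.025; dropout 20% (53 × 0.8 = 42.4, so about 42 completers per arm).

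**Inputs assumed.** Two-sided testing (sidedness is not stated); ICC 0.01 to 0.10; 3 to 10 clinics per arm. The article gives no value for these.

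**1. The article's own figure.** The 106 cannot be reproduced, because the difference, standard deviation, ICC and number of clinics behind it are not given.

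**2. The sample-size formula already contains the missing factor.** The article inflates n to N = nk(1−ρ)/(k−nρ). Taking n, N and k per arm, this rearranges to N = n[1+(N/k−1)ρ]. With m = N/k participants per clinic, that is inflation by the usual design effect, DE = 1+(m−1)ρ. The true variance of the arm difference is larger than the t test assumes by about this same DE.

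**3. Actual type I error of the planned t test.** It equals 2 × [1 − Φ(2.2414/√DE)], where 2.2414 is the two-sided 0.025 critical value. Example: 53 per arm in 5 clinics gives m = 10.6. With ICC 0.05, DE = 1 + 9.6 × 0.05 = 1.48, then 2.2414/1.2166 = 1.842, and the rate is 6.5%.

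| Clinics per arm | n per arm | m | ICC 0.01 | ICC 0.02 | ICC 0.05 | ICC 0.10 |
|---|---|---|---|---|---|---|
| 3 | 53 | 17.7 | 3.8% | 5.2% | 9.8% | 17.0% |
| 4 | 53 | 13.25 | 3.4% | 4.5% | 7.8% | 13.3% |
| 5 | 53 | 10.6 | 3.2% | 4.0% | 6.5% | 10.9% |
| 10 | 53 | 5.3 | 2.8% | 3.2% | 4.2% | 6.1% |
| 10 | 42 | 4.2 | 2.7% | 3.0% | 3.7% | 5.1% |

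At ICC 0 every row is 2.5%.

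**4. Simulation under the null.** With 10 equal clinics of 11 participants in total (40,000 trials per setting), the rates were 3.2%, 4.1%, 6.7% and 11.6% at the four ICCs, in line with the formula.

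**5. Unequal clinic sizes.** I simulated 5 clinics per arm with a coefficient of variation in size of 0.7 (20,000 trials per setting). With 42 per arm the rates were about 7% (ICC 0.05) and 12.5% (ICC 0.10), against 5.6% and 9.0% for equal sizes. With 53 per arm they were about 9% and 15%.

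**6. Can the sensitivity check catch it?** A simulated analysis-of-variance test for clustering at the 5% level detected a true ICC of 0.05 in about 14% of trials (10 clinics, 42 per arm) to 25% (5 clinics, 53 per arm). For ICC 0.10 it was about 27% to 48%. Absence of a clustering signal would be weak evidence that the plain t test is safe.

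**7. Does respecting clinic restore the level?** A t test on clinic means, equal sizes, gave 2.4% to 2.7% in every setting from 6 to 20 clinics in total and ICC 0 to 0.10.

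**The case against.** The strongest points on the other side are these.

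- **The excess depends on an unstated ICC.** True. At ICC 0.01 with many clinics it is trivial (2.7%). The tested variable is also a change score, which removes stable baseline differences between clinics, so its ICC may differ from that of raw scores. It does not remove differences in how clinics rehabilitate over the 12 weeks, which is where clustering of change would arise.
- **The nominal level is not settled.** The 0.025 has no sidedness, and Adaptive design modification criteria foresees a Bonferroni adjustment following the initial interim analysis. Neither point rescues the test. In the worked example (DE 1.48), a one-sided 0.025 gives 1 − Φ(1.960/1.2166) = 5.4%. A two-sided threshold halved to 0.0125, taken as an illustration, gives 2 × [1 − Φ(2.498/1.2166)] = 4.0%. That is 3.2 times nominal, against 2.6 times at 0.025.
- **The authors foresaw clustering.** They did, in the sample size and in a sensitivity analysis, and the article does not say that a null check would justify the t test. But inflating the sample does not change the standard error the t test computes, and a sensitivity analysis does not replace the result on which the conclusion rests.
- **A separate analysis plan may exist.** The article did not leave the test open. It named one that conflicts with its own design.

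What stands is that the size is uncertain and could be small. The conflict between the randomised unit and the test remains.

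**Conclusion.** The analysis is wrong as written. Clinics are the randomised units, the sample-size formula carries a design effect, and the main test sets that design effect to 1. For any positive ICC, with more than one participant per clinic, the type I error exceeds the stated level for both main outcomes. The direction does not depend on the assumptions; the size does. Under the ICCs and clinic numbers assumed here it runs from barely above nominal to several times nominal, and ICC 0.05 with 5 clinics per arm gives 6.5%, or 2.6 times 0.025. Because this is the confirmatory test of the trial, it should be corrected before the final analysis.

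**What to change.** Replace the main test in Data analysis with one that accounts for clinic:

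- **Primary model.** For each main outcome, a linear mixed model with arm as a fixed effect and clinic as a random intercept, using Satterthwaite degrees of freedom (available in SPSS MIXED). This can be applied to the change score as now planned. Modelling the 12-week value with the baseline value as a covariate is also reasonable, but it is a separate choice and not needed to cure this problem.
- **Few clinics.** If clinics per arm are very few, use a t test on clinic-level summaries. Fix the number that triggers this before arm-level results are seen. The simulations above tested this analysis, not the mixed model.
- **Secondary outcomes.** Use the same model for those planned for t tests. The scales planned for chi-squared tests need a categorical method that allows for clinic, or a clinic-level comparison; the linear model does not carry over directly.
- **Plain t test.** Keep it, if wanted, as a sensitivity analysis.
- **Reporting.** State the number of clinics, the assumed ICC and the sidedness of the test.

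No new data are needed, and recruitment was still under way when the article was written. Confidence intervals will be wider. With few clinics the degrees of freedom are small (8 for clinic means from 5 clinics per arm), so power may fall below 0.80. Whether 106 is enough cannot be judged from the article; the interim recalculation should assume the analysis that will actually be used.
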